**Fig. 3 Fig3:**
[figure not shown]
SPIRIT diagram: schedule of enrollment, interventions, and assessments

Table 1 provides a description of all study measures completed by participant dyads to assess primary and secondary outcomes and mechanisms of change. Measures with accessible versions in the Spanish language will be used, and if not, will be translated into Spanish.

**Table 1 Tab1:** Effectiveness outcomes: study assessments for primary, secondary, and mechanisms

Construct	Measure	Data Source	Timepoint
*Primary outcome*	**Engagement in CSC Family Psychoeducation (Aim 1)** will be measured as first session attendance rate and total attendance rate per family	Administrative data	Monthly
	**Engagement in FAMES (Aim 2)** will be measured by FAMES session attendance rate and the total number of contact minutes with participants by videoconference, in-person, and phone, and # of encounters by email, and text	Family peer survey	Weekly
*Secondary family outcomes*	**Perceived Stress (Aim 1)** will be assessed using the *Perceived Stress Scale*, which contains 10 Likert-style items to assess the degree to which an individual appraises life as stressful	Family participant survey	BL, 3 m, FU
	**Anxiety (Aim 1)** will be assessed using the *General Anxiety Disorder-7 item* [64]*.* Scores 8 or greater is cut-off for anxiety disorder	Family and client participant survey	BL, 3 m, FU
*Secondary client outcomes*	**Client Engagement in CSC (Aim 1)** will be measured as the client attendance rate in CSC	Administrative data	Monthly
	**Depression (Aim 1)** will be measured using the *Patient Health Questionnaire-9 item* [65]. A score of 10 or greater is cut-off for depression	Client participant survey	BL, 3 m, FU
	**Psychosis (Aim 1)** will be measured using *Community Assessment of Psychic Experiences – Positive 15-items Scale* [66]	Client participant survey	BL, 3 m, FU
*Mechanisms*	**Self-Efficacy (Aim 2)** will be measured using the 10-item *General Self-Efficacy scale* [67]. Scores range from 10 to 40, with higher scores indicating greater self-efficacy	Family participant survey	BL, Monthly
	**Connectedness (Aim 2)** will be assessed using the *Social Connectedness subscale of YSS-F* [68, 69], which assesses social support. Scores range from 4–20 where higher scores indicate greater social connectedness	Family participant survey	BL, Monthly

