### Data analysis plan

All analyses will follow an intention-to-treat principle with participant data within clusters analyzed according to the cluster’s randomized crossover time. All quantitative analyses will utilize a type I error rate of *p* < 0.05. Multiple imputation will be used for missing secondary psychological outcomes, with separate imputations conducted by study phase and clinic, incorporating demographic variables to ensure the accuracy of imputed values under the assumption of missing at random. Analyses will be conducted using STATA version 14.2, R statistical software, or the Statistical Package for the Social Sciences (SPSS, version 31.0).

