#### Aim 1: Impact of FAMES on primary and secondary outcomes

##### Quantitative data analysis

Statistical analyses for primary engagement outcomes will use Generalized Linear Mixed Models (GLMM) to compare engagement rates between the control (ACC) and intervention (FAMES), with a random effect for cluster (site), a fixed effect for each phase (ACC and FAMES), and a fixed effect for implementation wave to control potential time-related confounding [80, 81]. GLMM will also be used to assess change scores on secondary outcomes for family member and client participants from baseline to 3 months. Restricted maximum likelihood estimation with Kenward-Roger standard error and degrees of freedom correction to accommodate for our relatively small number of clusters will be used. Supplemental analyses will assess the likelihood of including relevant individual and program covariates (e.g., age, biological sex, race, and others) in models if significant differences among covariates occur between ACC and FAMES samples. Analysis of the secondary outcomes collected only from FAMES participants at follow-up will employ GLMMs to compare baseline to 3-month to follow-up inventory scores as a random effect repeated measures factor. Fixed effect covariates (e.g., age, biological sex, race, and others) will be included in these models as appropriate. A Bonferroni correction will be applied to primary engagement outcomes (first session attendance and total attendance per family and client) to control for multiple testing.

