### Power analysis

All power analyses were conducted with G*Power v. 3.1 [87], using different potential sample and effect sizes, assuming nine CSC sites, and three waves to estimate the power to detect effects. Power estimations for Aim 1 focused on engagement primary outcomes. Using the design effect approach in the Shiny-CRT power estimation application [88], a sample size of 450 participants, with an effect size of 0.5, at a 2-sided alpha level of 0.025, and assuming an ICC in each period of 0.01, the estimated power to detect a significant difference between ACC and FAMES conditions for the primary outcome of engagement would exceed 85%. For specific to Aim 2, power analyses assumed a conservative *R*^2^ value of 0.10 for predicting engagement from seven Block 1 control variables. Based on a sample of 225 family member participants in the FAMES condition, at a two-sided alpha level of 0.05, estimated power would be 98% when assessing whether *R*^2^ differed significantly from zero. With the addition of three Block 2 mediator variables (change in inventory scores), if *R*^2^ was to increase to 0.20 so that the change in *R*^2^ is 0.10, with an adjustment to the two-sided alpha to 0.025 due to multiple hypothesis tests and potential correlation between Block 1 and 2 predictors, and an adjusted effect size for Block 2 change given Block 1 variables [89] power would increase to 99% to detect a significant change in *R*^2^. Estimated power to achieve significant differences in implementation outcomes (i.e., pre- and post-change in knowledge) assumed a standardized mean difference of 0.60. Based on a sample of 20 family peer and provider participants, at a one-sided alpha level of 0.05, and a correlation among repeated measures of 0.50, estimated power would be 83% to establish significant change in knowledge. As such, this study is sufficiently powered (> 80% power) to detect meaningful differences in engagement outcomes, mediation effects, and knowledge, with adjustments for clustering and the stepped-wedge design structure.

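### Bonferroni for the primary engagement outcomes is valid but inefficient: Holm's step-down gives the same 5% family-wise control and never rejects less

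*Protocol article*

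**What the plan says.** The protocol article, Data analysis plan, sets a general level of 0.05: "All quantitative analyses will utilize a type I error rate of" p < 0.05. The Aim 1 quantitative analysis then states that "A Bonferroni correction will be applied to primary engagement outcomes", and lists these as "first session attendance and total attendance per family and client) to control for multiple testing". No step-down or other sequential procedure is mentioned.

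Table 1 gives the Aim 1 primary outcome, engagement in family psychoeducation, as two measures: it "will be measured as first session attendance rate and total attendance rate per family". Client engagement is a separate row under secondary client outcomes and "will be measured as the client attendance rate in CSC".

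The Power analysis section takes "a sample size of 450 participants, with an effect size of 0.5", an intracluster correlation of 0.01, nine sites and three waves, "at a 2-sided alpha level of 0.025", and reports power above 85%. The 0.025 equals 0.05/2, so the calculation assumes two tests.

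**The concern.** Single-step Bonferroni tests each of the two outcomes at 0.025 whatever the other one shows. Holm tests the smaller p-value at 0.025 and, if that is significant, the larger at 0.05. Both procedures keep the family-wise error at or below 5% under any dependence between the tests. Once one outcome has been rejected, holding the other at 0.025 costs power and buys no extra family-wise protection.

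The two measures answer different questions: whether a family starts psychoeducation, and how much of it the family attends. With p-values of 0.01 and 0.04, for example, the plan as written must call the second measure negative, whereas Holm would declare both positive.

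The article fixes this choice in its text, so it is not a detail left to an analysis plan that is not shown.

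**Working it through.** **Inputs from the protocol.** Effect size 0.5; 450 participants, 225 per condition; nine sites, three waves; ICC 0.01; two-sided 0.025 per test; stated power above 85%.

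**Assumptions.** The correlation between the two test statistics is not given, so 0.3 to 0.8 is used. Unless stated otherwise, both outcomes have the same effect size.

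**Step 1: reproduce the stated power.** Take a standard stepped wedge with nine clusters, three sequences and four periods. That is 36 cluster-periods with 450/36 = 12.5 participants each. With SD 1 and the Hussey-Hughes generalised least squares variance, the standard error is 0.1505.

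- Noncentrality: 0.5/0.1505 = 3.32.
- Power at two-sided 0.025: Φ(3.322 − 2.241) = Φ(1.081) = 86.0%, which agrees with the stated figure.
- Power at two-sided 0.05: Φ(3.322 − 1.960) = Φ(1.362) = 91.3%.

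Holm's gain per outcome is therefore at most 91.3 − 86.0 = 5.3 points. It falls short of that because the 0.05 level opens only after the other outcome is rejected.

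**Step 2: compare the procedures.** Correlated normal test statistics with noncentrality 3.32 were simulated. Bonferroni rejects outcome i if p_i ≤ 0.025. Holm requires min(p₁, p₂) ≤ 0.025 and then rejects every outcome with p_i ≤ 0.05.

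| Correlation | Per outcome, Bonferroni | Per outcome, Holm | Both, Bonferroni | Both, Holm | At least one (either method) |
|---|---|---|---|---|---|
| 0.3 | 86.0% | 90.1% | 75.7% | 84.0% | 96.3% |
| 0.5 | 86.0% | 89.8% | 77.2% | 84.8% | 94.8% |
| 0.8 | 86.0% | 89.0% | 80.4% | 86.5% | 91.6% |

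No scenario contained a rejection by Bonferroni that Holm missed. With no effect on either outcome, the two methods have the same family-wise error: 4.9% at correlation 0, about 4.7% at 0.5 and 4.0% at 0.8.

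**Step 3: vary the assumptions.**

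- *Smaller second effect.* If it is 0.4, power for that outcome rises from 66% to 74%; if 0.3, from 40% to 50-51%. These effect sizes are illustrations and do not come from the protocol.
- *Higher true power.* A parallel design-effect calculation gives 1 + (50 − 1) × 0.01 = 1.49. The noncentrality is 0.5/√(2 × 1.49/225) = 4.34, and power at 0.025 is 98.2%. This also exceeds 85%. At correlation 0.5 Holm then moves power per outcome only from 98.2% to 99.0%.
- *Lower true power.* At 71% per test, the chance that both are significant rises from 54-62% to 66-71%.
- *More tests.* With three tests, power per test rises from about 82% to 87-89%; with four, from about 79% to 85-88%. Under plain Bonferroni, going from two tests to four lowers power from 86.0% to 79.5%, a drop of 6.5 points.

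**The case against.** The strongest reply is that nothing in the plan is wrong. Bonferroni controls the family-wise error, the sample size was planned at 0.025, the stated power reproduces, and much the same suggestion could be made to almost any trial that uses Bonferroni. All of that stands. It makes this an efficiency point, but gives Bonferroni no advantage in error control or power.

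A reader might infer more than the documents support:

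- *That the trial's main claim loses power.* It does not. Power to show an effect on at least one primary outcome is identical under both methods. The larger gain, for both outcomes, matters only to the extent that both results are wanted; the protocol does not require both to succeed.
- *That the link between the outcomes makes the loss worse.* A family that never attends a first session has zero total attendance, so the two are related. But Holm does not exploit dependence. At equal effects the gain for both being significant shrinks from 8.3 points at correlation 0.3 (84.0 − 75.7) to 6.1 at 0.8 (86.5 − 80.4).
- *That the choice of procedure is the main multiplicity issue.* The number of tests matters at least as much. The Aim 1 text speaks of family and client, which could mean three or four tests, while Table 1 makes client attendance secondary and 0.025 implies two.

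One practical advantage of Bonferroni is real: it comes with matching 97.5% simultaneous intervals. Under Holm, ordinary 95% intervals can conflict with the decision. If both p-values are 0.03, neither outcome is rejected, yet both intervals exclude no effect.

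**Conclusion.** The point holds as an inexpensive improvement, not as the correction of an error. That Holm rejects at least as much as Bonferroni at the same family-wise level is a general result and depends on no assumption about this trial.

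The size of the gain does depend on assumptions. With 86% power per test, equal effects and correlation 0.3 to 0.8, it is about 3 to 4 points per outcome and about 6 to 8 points for both outcomes. It is larger if the second effect is smaller or true power is lower, and about 1 point per outcome if true power is near 98%. The extra rejections for two tests arise only when one p-value is at or below 0.025 and the other lies between 0.025 and 0.05.

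**What to change.** In the Aim 1 quantitative analysis, replace the Bonferroni correction with Holm's step-down procedure at family-wise two-sided alpha 0.05 for the primary engagement outcomes.

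In the same sentence, list the tests in the family. The two per-family measures in Table 1 match the 0.025 in the power section. The mention of the client must be reconciled with the secondary status of client attendance in Table 1. If client outcomes are meant to be in the family, the power section needs the corresponding first-step level.

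With two tests, the sample size and the 0.025 stay as they are, the latter as Holm's first step. State that the 95% confidence intervals are unadjusted and that the Holm decision governs the claim of significance.

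The cost is one or two sentences and somewhat less simple simultaneous intervals. Recruitment began in May 2025 and is expected to end in October 2029, so the amendment can be made without reference to outcome data by condition.

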#### Aim 2: Assess whether target mechanisms mediate FAMES engagement

##### Quantitative data analysis

To examine whether potential mechanisms (connectedness, self-efficacy, and motivation) mediate engagement in FAMES, hierarchical linear regression (HLR) will be used, with predictor variables entered in sequential steps. Demographic variables (age, gender, biological sex, race, ethnicity, years of education, employment status, marital status, clinic), will be entered in Block 1, followed by changes in mediator variables in Block 2. The unique contribution of each mediator will be assessed using changes in adjusted R2, and only significant predictors will be retained in the final models. Regression assumptions will be evaluated using variance inflation factors (multicollinearity) and Durbin-Watson statistics (independence of errors). To explore potential nonlinearity, alternative specifications such as interaction terms or polynomial transformations may be tested.

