### Research objectives and aims

Informed by the Health Equity Implementation Framework which explicitly focuses on equitable implementation of interventions to address inequities in care [45], the overarching goal of this study is to improve family engagement in CSC and address disparities in engagement. To accomplish this, the present study has three aims: (1) to evaluate whether integrating FAMES improves family member/support person engagement in CSC compared to an attention control condition (ACC); (2) to examine whether target mechanisms of connectedness, self-efficacy, and motivation mediate FAMES engagement among family members/support persons; and (3) to assess the impact of FAMES on reach, adoption, implementation, and maintenance using a concurrent mixed-methods approach.

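### Aim 2 is presented as a mediation analysis, but the planned regression can show only an association among FAMES recipients, and the stated power is for that association.

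*Protocol article*

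**What the plan says.** All references are to the protocol article.

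- **Aim.** Research objectives and aims states the second aim as "to examine whether target mechanisms of connectedness, self-efficacy, and motivation mediate FAMES engagement among family members/support persons".
- **Outcome.** Table 1 assigns Aim 2 its own outcome, engagement in FAMES, which "will be measured by FAMES session attendance rate and the total number of contact minutes", plus counts of email and text encounters. Family peers record it weekly. Engagement in CSC family psychoeducation is listed separately, for Aim 1.
- **Sample.** The Aim 2 calculation in Power analysis is "Based on a sample of 225 family member participants in the FAMES condition".
- **Model.** The Aim 2 analysis section states: "To examine whether potential mechanisms (connectedness, self-efficacy, and motivation) mediate engagement in FAMES, hierarchical linear regression (HLR) will be used". It enters demographic variables and clinic in Block 1, "followed by changes in mediator variables in Block 2". The interval over which change is taken is not given.
- **Criterion.** "The unique contribution of each mediator will be assessed using changes in adjusted R2, and only significant predictors will be retained" in the final models.
- **Power.** Power analysis gives 98% for a Block 1 R² of 0.10 and 99% for a Block 2 increase to 0.20. Its closing sentence counts mediation effects among the things the study is sufficiently powered to detect.

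**The concern.** A mediator carries the effect of an exposure to an outcome. A mediation analysis therefore needs an exposure contrast, an effect of the exposure on the mediator, an effect of the mediator on the outcome, and an estimate of the indirect path. The Aim 2 plan has at most one of these, the association between mechanism change and outcome.

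The choice of outcome makes an exposure contrast impossible, because control families have no FAMES sessions to attend. The outcome is also the amount of intervention received. FAMES is designed to act on these same mechanisms, so a family that attends more may gain more connectedness, self-efficacy or motivation because it attended. That gives the same positive coefficient as the hypothesised direction, and nothing in the stated model separates the two.

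At stake is the conclusion of one of the trial's three aims. As written, correlates or consequences of attendance could be reported as mechanisms of change, supported by a power statement that seems to cover that claim. Keeping only significant predictors adds selection: the final model would show the mechanisms that passed and omit those that did not.

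**Working it through.** **1. The elements of mediation against the text**

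| Element | Aim 2 as stated |
|---|---|
| Exposure contrast | None; FAMES condition only (Power analysis) |
| Effect of FAMES on the mechanisms | Not tested in the Aim 2 section |
| Mechanism related to outcome | Yes; Block 2 change scores |
| Indirect effect | None; change in adjusted R² instead |
| Mechanism change before outcome | Not stated |

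FAMES runs for 12 weeks (FAMES intervention section). Mechanisms are measured at baseline and monthly, and engagement weekly (Table 1). The data would allow a lagged analysis, but the text does not specify one.

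**2. Reproducing the stated power**

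Noncentral F test with λ = f² × N and N = 225. The R² values, numbers of predictors and alphas are from Power analysis.

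- Block 1: f² = 0.10 / 0.90 = 0.111; λ = 25; df 7 and 217; alpha 0.05. Power 96.9% (stated 98%).
- Block 2: f² = 0.10 / (1 − 0.20) = 0.125; λ = 28.1; df 3 and 225 − 10 − 1 = 214; alpha 0.025. Power 99.3% (stated 99%).

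The Block 2 figure is right as arithmetic. It is the probability of detecting that three change scores add 0.10 to R². No exposure effect or indirect effect enters the formula.

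**3. What the Block 2 test does when the mechanisms have no effect on engagement**

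Simulation: N = 225, seven covariates explaining 10% of engagement, 3,000 runs per setting, joint F test of three change scores at 0.025. Each change score is set to r × engagement + √(1 − r²) × noise, so engagement drives change and never the reverse. The values of r are assumptions, since the document gives none.

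| Assumed r | Mean sample R² increase | Test significant |
|---|---|---|
| 0 | 0.012 | 2.7% |
| 0.1 | 0.035 | 40.5% |
| 0.2 | 0.098 | 97.9% |
| 0.3 | 0.192 | 100% |

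This can be checked without simulation. Given the covariates, engagement has variance 0.9, so the three change scores give f² = 3 × r² × 0.9 / (1 − r²). At r = 0.1, 0.2 and 0.3 this is 0.027, 0.1125 and 0.267. The noncentral F of step 2 then gives 40.7%, 98.5% and over 99.9%.

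At r = 0.2 the average R² increase is close to the 0.10 that the protocol plans to detect.

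**4. Unmeasured common cause, again with no mechanism effect**

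If a shared cause explains 10%, 20% or 30% of the variance in each change score and of the covariate-adjusted variance in engagement (assumed values), the test is significant in 35.5%, 95.4% and 100% of runs.

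**The case against.** Several points on the other side are sound.

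- **Timing.** A reader might infer that mechanism change and engagement are measured over the same months by design. The article does not say so. It gives no change interval, and such a detail may sit in a fuller document. Reverse causation is therefore a possibility left open, not a feature fixed by the text. A lag alone would still not make this mediation, because there would be no exposure contrast.
- **Size.** A reader might infer that the test would declare false mediation 99% of the time. That holds only if reverse causation is assumed to produce the full R² increase of 0.10. The honest statement is the range in the working, from the nominal rate to certainty, according to an unknown correlation.
- **Control data.** A reader might infer that half the data are wasted. Control families' psychoeducation attendance is the comparator for the Aim 1 primary outcome, and nothing says that their mechanism scores will be discarded. They cannot enter an analysis whose outcome is FAMES attendance.
- **The question itself.** Table 1 separates FAMES engagement from CSC engagement on purpose. Asking what accompanies engagement with FAMES is a legitimate process question.
- **Selection.** The joint Block 2 test does not depend on which predictors are later kept, so dropping terms affects the reported final model and not that test.
- **A full redesign.** A reader might conclude that Aim 2 must become a 450-family mediation model. That would replace the investigators' outcome and rest on a weak contrast. With waves three months apart, 18 months of control and three of pre-implementation, wave 1 starts FAMES at month 21, while control recruitment ends at months 18, 21 and 24. Only months 21 to 24, wave 1 against wave 3, have both conditions recruiting together. The rest is before-after, in nine clusters.

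None of this supplies the missing exposure contrast or indirect effect, or makes the closing power claim correct.

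**Conclusion.** The point stands in a limited form. The article itself fixes the outcome, sample, model and criterion for Aim 2, and together they support only a within-FAMES association. Calling it mediation, and claiming adequate power for mediation effects, is wrong as written, and no other section repairs it.

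The conclusion about what the model can show needs no assumption beyond the text. The size of any misleading result depends on assumed correlations: none beyond the nominal rate at 0, about 40% at 0.1, and almost always at 0.2 or more. The documents do not show which of these applies. The Aim 1 comparison of control and FAMES is unaffected.

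**What to change.** 1. In the Aim 2 objective and analysis section, describe the regression as an exploratory within-FAMES association analysis.
2. State the change interval and put it before the outcome: for example, mechanism change from baseline to month 1 against engagement after month 1.
3. Keep all three mechanisms in the final model, in place of the rule that "only significant predictors will be retained in the final models".
4. In Power analysis, state that 99% is power for an R² increase of 0.10, and remove mediation effects from the closing sentence.
5. If a mediation claim is to be kept, add a secondary model of condition, then early mechanism change, then later CSC family psychoeducation attendance. Include site and calendar-time terms and the baseline mechanism score, an interval for the indirect effect suited to nine clusters, and a sensitivity analysis for mediator-outcome confounding. Data collection procedures has both conditions assessed at baseline and months 1 to 3, and Table 1 records psychoeducation attendance monthly, so no new data are needed.

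Items 1 to 4 need only changes of wording and a small change of model, and recruitment is expected to run to October 2029. The cost is a weaker Aim 2 conclusion. For item 5, power cannot be computed from the document, because it gives no effect size for either path, and the condition contrast would be largely before-after.

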	**Motivation (Aim 2)** will be assess using the 26-item *Treatment Motivation Questionnaire t*o assess motivation about services	Family participant survey	BL, Monthly

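### The Aim 2 regression enters each mechanism's change without its baseline score, so the change coefficients can pick up baseline effects with the sign reversed

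*Protocol article*

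**What the plan says.** The quantitative analysis section for Aim 2 describes a hierarchical linear regression of engagement in FAMES. It gives a closed list for the first step: "Demographic variables (age, gender, biological sex, race, ethnicity, years of education, employment status, marital status, clinic), will be entered in Block 1". The order of entry is that these variables "will be entered in Block 1, followed by changes in mediator variables in Block 2", and the second step is described no further.

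The Power analysis section describes the same model: "With the addition of three Block 2 mediator variables (change in inventory scores", and so on. The sample is the FAMES cohort alone: "Based on a sample of 225 family member participants in the FAMES condition". The section takes R² = 0.10 from seven Block 1 variables, a further R² gain of 0.10 from Block 2, and alpha 0.025, and states 99% power.

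Table 1 schedules all three mechanisms at baseline and monthly, so the baseline scores will exist. Nothing in the article places them in the Aim 2 model. The covariate rows of Table 1 cover individual, contextual and program characteristics. The optional alternative specifications for Aim 2 are interactions and polynomials, offered to explore nonlinearity.

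**The concern.** A difference score contains its own baseline with a minus sign. Families who start high tend to show smaller gains, and families who start low tend to show larger ones, even if the intervention does nothing to the mechanism. Starting motivation, self-efficacy or connectedness may also predict how many FAMES contacts a family takes up. If so, the omitted baseline confounds the association between change and engagement, and it works against a positive change effect.

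Two errors become possible. A mechanism that does matter can be diluted or cancelled. Alternatively, a mechanism whose change is irrelevant can appear significant with a negative sign, as if families who improved engaged less. Aim 2 exists to say which mechanisms matter, and Table 1 lists engagement in FAMES under primary outcome, so either error would affect a main conclusion of the trial.

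**Working it through.** **Inputs from the article.** N = 225; seven Block 1 variables with R² = 0.10; three Block 2 change scores; R² gain 0.10; alpha 0.025; stated power 99%.

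**Assumed, because the article does not give them.** The baseline to 3-month correlation rho (0.3, 0.5, 0.7) and the share of engagement variance explained by the three baselines together (0, 0.03, 0.05, 0.10). Variances are equal at the two times and the three mechanisms are independent.

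**1. The plan's own figure.** f² = 0.10/(1 - 0.20) = 0.125. With 10 predictors the F test has 3 and 225 - 10 - 1 = 214 degrees of freedom. With non-centrality 0.125 × (3 + 214 + 1) = 27.25, power is 99.1%. With the convention 0.125 × 225 it is 99.3%. The stated 99% reproduces either way. The first convention is used below; the second moves no power figure by more than 2 points.

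**2. Correlation of change with baseline.** For D = M3 - M0 with unit variances, cov(D, M0) = rho - 1 and var(D) = 2(1 - rho). The correlation is therefore -√((1 - rho)/2): -0.59, -0.50 and -0.39 for rho = 0.3, 0.5 and 0.7.

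**3. Masking.** Suppose engagement depends on the 3-month level, engagement = b × M3. The slope on D alone is b(1 - rho)/(2(1 - rho)) = b/2, half the coefficient obtained with baseline in the model. Let B be the R² of the three 3-month levels. The R² gain is B(1 - rho²) given baseline and B(1 - rho)/2 for change alone. Setting B(1 - rho²) = 0.10:

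| rho | B | change-only gain | change-only power | power with baseline in Block 1 |
|---|---|---|---|---|
| 0.3 | 0.110 | 0.038 | 64% | 99.1% |
| 0.5 | 0.133 | 0.033 | 56% | 99.2% |
| 0.7 | 0.196 | 0.029 | 49% | 99.6% |

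For example, at rho = 0.5, f² = 0.0333/(1 - 0.1333) = 0.0385 and the non-centrality is 0.0385 × 218 = 8.4.

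**4. False rejection.** Suppose change has no effect and the baselines jointly explain R0. The change scores then pick up a population R² gain of R0(1 - rho)/2, with negative coefficients if higher baseline means more engagement. At rho = 0.5 and R0 = 0.10 this is 0.025. Simulated rejection rates for the Block 2 test at nominal 2.5% (3,000 replicates):

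| R0 | rho = 0.5 | rho = 0.7 |
|---|---|---|
| 0.03 | 10% | 8% |
| 0.05 | 19% | 11% |
| 0.10 | 40% | 23% |

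Repeat runs differed by up to about 2 points; the lowest value seen was 7%. At R0 = 0 the rate was 2.3%. With the three baselines in Block 1 it stayed at about 2% to 3% throughout.

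**5. Cost of adjusting when only change matters.** If the change scores truly give a gain of 0.10 and baseline adds nothing, the gain conditional on baseline is 0.10(1 + rho)/2 = 0.065, 0.075 and 0.085. With 13 predictors (3 and 211 degrees of freedom), power is 91.3%, 95.1% and 97.3%.

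**The case against.** **The meaning of change is not fixed.** The article never says raw difference. Change could be a residualised score, which already conditions on baseline, or a slope over the monthly scores. This stands in part: a residualised score would remove the problem. But change in inventory scores is most naturally read as a difference, and the article spells out the rest of the model, including a closed Block 1 list.

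**A reader might infer that the stated 99% power is wrong.** It is not. The Power analysis section assigns the R² gain of 0.10 to the change scores themselves, and the arithmetic is right. The 49% to 64% arises only if the 0.10 is assigned to the baseline-adjusted gain and the 3-month level drives engagement.

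**A reader might infer that ceilings on the scales are a separate cause.** The scales are bounded (for self-efficacy, "Scores range from 10 to 40, with higher scores indicating greater self-efficacy"), but the article gives no baseline means. In a single-mechanism simulation at rho = 0.5 with a baseline association of 0.3, false rejection was 51.5% without a ceiling and 47% with one at +1 SD. A ceiling with no baseline-engagement link gave 2.8%. Ceilings add nothing that these checks can support.

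**A reader might infer that the model would falsely confirm a hypothesised mechanism.** If higher baseline goes with more engagement, the spurious coefficients are negative, so they would contradict the hypothesis. Masking is the stronger half of the concern.

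**The size rests on unseen inputs.** This stands. No passage shows that baseline predicts engagement, and without that link there is no excess error.

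**Adjustment is not a full cure.** This also stands. With measurement reliability of 0.85 and a baseline association of 0.3, false rejection at rho = 0.7 fell from 21% to 6%, not to 2.5%. Engagement is logged over the same 12 weeks in which change is measured, so reverse direction remains possible under either model.

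**Conclusion.** The concern holds as a fault in the specified model. Baseline mechanism scores are collected, are left out of a closed covariate list, and are negatively correlated with the change scores by construction. If baseline predicts engagement, the Aim 2 coefficients are biased with reversed sign. When change has no effect, false rejection is about 7% to 40% against a nominal 2.5%, for rho of 0.5 to 0.7 and joint baseline R² of 0.03 to 0.10. When the 3-month level drives engagement with a baseline-adjusted gain of 0.10, power is about 49% to 64% for rho of 0.3 to 0.7. These are ranges under assumed inputs, with equal variances and independent mechanisms, and are not predictions for this trial. If baseline is unrelated to engagement, the error rate is nominal. The article gives no reason to expect that, and protection is nearly free, so the model should be changed.

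**What to change.** In the Aim 2 analysis, add the baseline connectedness, self-efficacy and motivation scores to Block 1, and test the three changes in Block 2 conditional on them. Entering the 3-month scores in Block 2 with baseline in Block 1 gives the same test when change is the simple difference from baseline to 3 months. State how change is calculated and over which time points. Restate Block 2 power with the three extra Block 1 terms.

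The cost is a change of wording and three degrees of freedom. For an unchanged conditional gain of 0.10, power stays at about 99%. If only change matters, it falls to about 91% to 97%, still above the plan's 80%. No new data are needed. Each site spends 18 months on the control phase and 3 on pre-implementation, so its FAMES cohort starts 21 months after its own start date, which leaves time to amend. The amended text should not present baseline adjustment as evidence of mediation or as a complete remedy for measurement error.
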